##### Procedure for unblinding if needed {17b}

In this study, there are two unblinding provisions. The first unblinding is at the end of blind audit data locking, and the second unblinding is at the end of statistical analysis. According to the emergency unblinding regulations, when patients need to receive emergency treatment due to adverse events, and the emergency treatment is related to the actual situation of receiving the study drug, the project research leader and the project supervisor can decide to open the emergency unblinding and read the corresponding emergency letters. Researchers should fill in the corresponding records with the date, reason, and process of unblinding.

#### Data collection, management, and analysis

##### Data collection {18a}

The data involved in this project mainly include random grouping data, clinical baseline data, intervention symptoms and signs change, follow-up data, and results of statistical analysis data.

The random grouping data shall be provided by the researcher in charge of the random grouping of the project (random center) of Shanghai University of Traditional Chinese Medicine, and only the person in charge of each clinical research center has the right to obtain the data.

All clinical research centers are responsible for the diagnosis and screening of clinical baseline data, and the physicians are responsible for recording and collecting the data.

The person in charge of each clinical research center shall arrange full-time data collection personnel to collect the intervention symptoms, signs, and follow-up data. They shall not actively know the random grouping, intervention plan, and other information.

Statistical analysis results data are collected and provided by the researcher in charge of data statistical analysis (statistical center) of Shanghai University of Traditional Chinese Medicine, who do not know the random grouping and clinical intervention information. After clinical trial completion, the personnel from the “statistical center” will go to each clinical research center to find the person in charge of each subcenter to coordinate and collect the case observation form, record the observation form in the database, and lock it under the supervision of the general research director of the project and the project supervisor (not directly involved in the project research).

##### Plans to promote participant retention and complete follow-up {18b}

To ensure retention of participants, follow-up visits will be scheduled to coincide with routine clinic appointments as far as possible. The study staff will contact participants, either over the phone or WeChat, before their scheduled follow-up appointment, immediately after the first treatment; 3 days and 1, 2, 4, 8, and 12 weeks after the intervention; and at 26 and 52 weeks after treatment follow-up.

##### Data management {19}

Before the start of the project, a complete project research operation SOP, investigator manual, and case report form should be established, and work training and summary meetings should be held before the start of the project and in the middle of the project, with detailed training and explanation of the test scheme, research operation SOP, and investigator manual contents. The case observation director of each research center should be established, and the case study work micro should be established by the person in charge of each research center credit group: case observation doctors in charge of each center should take photos of collected cases in the working group of each center, and give them to the person in charge of the subcenter who should, on the day of receipt, upload the standardized filing of the collected case report form. Consequently, Shuguang Hospital, the responsible unit of the project, should assign a special case supervisor, who should establish a WeChat working group with the person in charge of each center, and the supervisor should spot check the case report form from each center at any time to fill in the specification. After the test, the researcher (statistical center) in charge of project data statistics and analysis, a full-time statistician of Shanghai University of Traditional Chinese Medicine, should collect the original data from the case report form of each subcenter, and under the supervision of the chief research director of the project and the project supervisor (not directly involved in the project research), the assistant should cooperate with two people to back up and input those case reports into an Excel form, mutually proofread and correct input errors, check the accuracy with the original data in the case report form, lock the data, and then conduct statistical analysis.

##### Confidentiality {27}

The medical records (CRF, report form, etc.) of the participants will be completely saved in the research center of the project. All the privacy data of the subjects are stored in encrypted protection, only to be seen by the main researchers of the project, only for the research of the project, not for other purposes.

#### Plans for collection, laboratory evaluation, and storage of biological specimens for genetic or molecular analysis in this trial/future use {33}

Not applicable in this study.

#### Statistical methods

##### Statistical methods for primary and secondary outcomes {20a}

Statistical results and data analysis are the responsibility of the researcher (Statistics Center) in charge of statistics and data analysis for the entire project, and the patients are divided into the following data sets according to different situations.

Full analysis set refers to the ideal set of subjects as close as possible to the intentional analysis principle (mainly including all randomized subjects). The data set is obtained after the elimination of the smallest and reasonable method among all randomized subjects. To estimate the missing value of the main variable, the last observation carried forward (LOCF) method is used to carry forward the missing part of the test data. The number of subjects in each group who evaluate efficacy at the end point is consistent with that at the beginning of the test.

Per-protocol set, all patients who meet the trial protocol, who use 80–120% of drugs, have good compliance, do not use prohibited drugs during the trial, and complete the CRF requirements.

Safety analysis set, all cases are randomly divided into groups, at least one use of study drug, or receive manual treatment, and at least one follow-up record, constitute the safety analysis population of this study. Safety population is the main population for safety evaluation in this study.

The main variables and the comprehensive efficacy analysis are the full analysis set and the compliance scheme set, respectively; the demographic and other baseline characteristics are the full analysis set; the safety evaluation is the safety set.

For continuous variables, the number of cases, mean, standard deviation, median, and minimum and maximum values will be listed; for classified variables, the form of frequency table (frequency and percentage) will be listed. Baseline is defined as the last observation data before the first treatment.

Specific statistical data analysis, using the latest SPSS statistical analysis software, first of all, paired *t* test statistical analysis is carried out for each group’s pre-treatment pain and the improvement of each group’s pain after treatment intervention, and single-factor analysis of variance is carried out for each group’s immediate, 3-day, 1-, 2-, 4-, 12-week pain after intervention; secondly, before treatment and immediately after treatment intervention, 3 days, 1, 2, 4, and 8 weeks. One-way ANOVA is used to analyze the cervical dysfunction index, cervical activity, overall improvement, and treatment satisfaction of patients at 12 weeks. All the statistical tests are double-sided, *P* < 0.05 would be considered statistically significant.

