### Inclusion criteria

Age range from 18 to 65 years.The subjects meet the above diagnostic criteria for acute and subacute neck pain.NRS score of ≥ 3.It is an axial (non-root) neck pain caused by changes in the facet joints, discs, muscles, and ligaments [1].Those who are willing to participate in this experiment and sign the consent letter.

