#### Outcomes {12}

##### Effectiveness evaluation index

The manual intervention program was pre-tested in our research group’s experimental study and was in effect immediately after the shortest treatment, and the longest treatment time was 12 weeks. Combined with the reported literature on related neck pain [14, 15], both groups are treated according to the main intervention methods of each group for a period of up to 12 weeks. Clinical data will be collected before the intervention and immediately after the first treatment; at 3 days and 1, 2, 4, 8, and 12 weeks after the intervention; and at 26 and 52 weeks after treatment follow-up of clinical observation index data collection. The clinical observation indexes are as follows: (1) cervical pain is the primary observation index, measured by NRS [16] and composed by a horizontal line with a length of 0–10 cm, and the anchor words are “0” for “no pain” and “10” for “extreme pain.” Participants are asked to select a point on the NRS line segment that corresponds to their current or recent week’s average pain intensity and draw a vertical line as a marker to express the pain intensity. The researchers determine the NRS score by measuring the distance from the starting point of “painless” to the marker point; the higher the score is, the stronger the degree of pain is. The specific judgment is as follows: 1–3 cm is mild pain, 4–6 cm is moderate pain, and 7–10 cm is severe pain. The secondary indices include the following: (2) cervical dysfunction index, measured by patient self-evaluation with cervical NDI [17, 18], which has 10 items in total, six options under each item, from light to heavy, corresponding to the score of 0–5, the lowest score of each item is 0, and the highest score is 5; the higher the score is, the more serious the degree of dysfunctions. NDI (%) = [(total score)/(number of items completed by subjects × 5)] × 100. The specific judgment is as follows: 0–20% indicates mild dysfunction, 21–40% indicates moderate dysfunction, 41–60% indicates severe dysfunction, 61–80% indicates extremely severe dysfunction, and 81–100% indicates complete dysfunction (whether subjects have exaggerated symptoms should be checked in detail); (3) cervical activity measurement [19], measured by the cervical vertebra mobility measurement program of Android mobile phone system, with a minimum of 5 degrees carry measurement; (4) overall improvement, measured by self-evaluation of patients with SF-36 (The Medical Outcomes Study 36-Item Short-Form Health Survey) [20, 21], which is composed of physical functioning, role-physical, bodily pain, general health, vitality (VT), social functioning (SF), role-emotional, mental health, and health transition; and (5) satisfactory treatment, determined by patient self-evaluation, is 1 of 3 levels: dissatisfied, satisfied, and very satisfied.

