#### Sample size {14}

In this project, the trial group and the control group are to be set up. This study is designed with the control group as the optimal design, and the results are summarized according to previous clinical trials and literature [2]. According to the results of previous clinical trials and literature summary, the first observation index after 12 weeks of treatment was NRS score of neck pain, 1.50 ± 1.70 in the trial group, 2.08 ± 1.65 in the control group; *α* = 0.05 (bilateral test), *β* = 0.10, boundary value 0.08, sample size ratio *k* = 1 in both groups. The PASS software is used to calculate the sample size of 102 cases in the two groups. Considering that the sample size loss rate is about 10–20%, further calculated the sample size of each group is *N* = 120.

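### LOCF is the only stated method for missing primary pain scores, in a condition the design expects to improve, so dropout biases the week-12 comparison

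*Protocol article*

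**What the plan says.** Outcomes {12} states that "cervical pain is the primary observation index, measured by NRS", scored from 0 to 10. Scores are taken before treatment, immediately after the first treatment, at 3 days, at weeks 1, 2, 4, 8 and 12, and later in follow-up. Sample size {14} is built on the week-12 score.

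In {20a}, under the full analysis set, missing values of the main variable are handled in one way: "the last observation carried forward (LOCF) method is used to carry forward the missing part of the test data". The next sentence is "The number of subjects in each group who evaluate efficacy at the end point is consistent with that at the beginning of the test", so carried scores enter the analysis as if they had been observed.

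Other parts of the protocol bear on this:

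- Section {20c}, whose heading covers missing data, names no other method. It asks for reasons to be recorded and for dropout and compliance to be compared between groups.
- Section {20b} rules out analyses beyond the main ones.
- The inclusion criteria require "NRS score of ≥ 3". The week-12 planning values in {14} are "1.50 ± 1.70 in the trial group, 2.08 ± 1.65 in the control group".
- On attrition, {14} says "Considering that the sample size loss rate is about 10–20" per cent, with no split by arm.
- The shedding criteria include continuing increase in pain. Section {11b} has patients whose severe pain prevents manipulation, or whose pain is not soon relieved, given emergency medication and then removed from the trial.

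**The concern.** LOCF estimates a week-12 mean without bias only if a leaver's score would have stayed where it was, or if the errors happen to cancel between arms. The design assumes the opposite of a flat course, because a patient who enters at 3 or more is expected to finish, on average, at about 1.5 or 2. A score carried from day 3 or week 1 therefore leaves out most of the expected improvement, and each leaver pulls that arm's mean upwards.

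If one arm loses more patients, or loses them earlier, the pull is unequal and appears as a treatment difference. If loss is equal, the arm that improves more loses more of its improvement, so a real difference is diluted. The primary efficacy comparison is exposed in both cases, and the planned difference of 0.58 points is small enough for modest distortions to matter.

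**Working it through.** **Planning figures.** The planned difference is 2.08 − 1.50 = 0.58. The loss allowance reproduces at 15%: 102 / (1 − 0.15) = 120 per group. The 102 itself does not follow from the stated inputs. With a pooled SD of √[(1.70² + 1.65²)/2] = 1.675, two-sided 0.05 and power 0.90, the need is 176 per group for a difference of 0.58, or 136 if the 0.08 boundary is added to give 0.66. That is a separate matter and does not affect this point.

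**Bias formula.** Let d be the dropout proportion and g the carried score minus the score the leaver would have had at week 12. Then the LOCF bias in (trial − control) is d_T·g_T − d_C·g_C.

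**Illustration with no true effect.** All of the following are assumptions: dropout of 10% in one arm and 20% in the other, carried scores of 3, 3.5 or 4, and a week-12 mean of 2 in both arms.

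- 0.10 × (3.0 − 2.0) = 0.10, and 0.10 / 0.58 = 17%
- 0.10 × (3.5 − 2.0) = 0.15, and 0.15 / 0.58 = 26%
- 0.10 × (4.0 − 2.0) = 0.20, and 0.20 / 0.58 = 34%

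**With the planned effect (−0.58).** Assume a baseline mean of 3 to 6 and a carried score that misses a fraction f = 0.5 to 1 of the improvement, so g_T = f·(baseline − 1.50) and g_C = f·(baseline − 2.08).

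| Dropout, trial / control | Bias | Direction |
|---|---|---|
| 10% / 20% | −0.02 to −0.33 | favours manipulation |
| 20% / 10% | +0.10 to +0.51 | against manipulation |
| equal, 10% to 20% | +0.03 to +0.12 | towards no difference |

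For example, at baseline 6 with f = 1 and 20% / 10%, the bias is 0.20 × 4.50 − 0.10 × 3.92 = 0.508. With equal dropout the baseline cancels and the bias is d·f·0.58; at most this is 0.20 × 1 × 0.58 = 0.116.

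**Simulation.** This used 4,000 runs, 120 per arm, exponential recovery, autocorrelated scores and last visits between 3 days and week 4. The shape of recovery, the correlation, the baseline and the dropout timing are all assumed.

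- No true effect, random dropout of 10% and 20% in either order: LOCF bias was about 0.13 in size at baseline 4 and 0.25 at baseline 6. Type I error was 8–10% and about 17%. An available-case week-12 comparison stayed within about 0.01 of the truth, with type I error of 5.1–5.4%.
- No true effect, same split, dropout related to week-1 pain: LOCF bias was about 0.15 at baseline 4 and 0.26 at baseline 6. The available-case estimate was then off by 0.04–0.05.
- True difference 0.58, equal random dropout of 15%: power was 0.63 (baseline 4) or 0.54 (baseline 6) with LOCF, 0.69 with available cases and 0.76 with no dropout.
- Standard error, no true effect, random dropout: the mean LOCF standard error matched the empirical SD of the estimator (0.224 against 0.222–0.228 at baseline 4; 0.248–0.249 against 0.246–0.252 at baseline 6). Interval coverage in the unequal-dropout runs fell to about 75–94%, because of bias.

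The mixed model proposed below was not itself simulated.

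**The case against.** **Size.** The strongest reply is that the size is conjecture. A reader might take 10% versus 20% to be the plan's own expectation by arm. It is not: {14} gives a range for overall loss only. With equal dropout and no true effect, the formula gives zero bias. No section links visit burden to dropout, and {11c} and {18b} plan retention measures. This stands, and the figures are illustrations.

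**Standard error.** A reader might also infer that treating carried scores as data makes the standard error too small. The working does not bear that out. Compared with an available-case standard error of 0.234–0.235, the LOCF value was smaller at baseline 4 and larger at baseline 6. What can be said is that uncertainty due to missing data is not reflected.

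**The immediate score.** It is tempting to picture a minutes-after-treatment score carried to week 12 in the manipulation arm. That assessment is scheduled in both arms and is carried only if every later visit to week 12 is missed. If relief is immediate, the carried score could also be low.

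**Mitigation.** Efficacy is also analysed per protocol, and the trial calls itself exploratory. The per-protocol set needs good compliance and completed forms, so it leans less on carried values. But it selects patients and does not test the LOCF assumption. Neither point removes the bias from the full-analysis-set result.

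**Remedy.** A missing-at-random model may predict improvement for patients removed because of rising pain. This stands, and it is why the sensitivity analysis is a necessary part of the fix.

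**Conclusion.** The point holds. LOCF is the only method the protocol states for missing primary scores. The entry floor and the expected week-12 means imply improvement over time, 10–20% loss is expected, and the shedding criteria and {11b} make some of that loss pain-related. Week-12 estimates based on carried early scores will be biased in a direction that cannot be fixed in advance if dropout is unequal, and towards no difference if dropout is equal and a true difference exists.

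The illustrative size is 0.10–0.20 points (17–34% of 0.58) with no true effect, and 0.03–0.12 points of attenuation with equal dropout and the planned effect. These rest on assumed carried scores or baseline, an assumed degree of missed improvement and, for the first, an assumed split by arm and week-12 mean. The documents do not support saying that manipulation is favoured, or that the standard error is too small. This should be changed before the data are locked.

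**What to change.** In {20a}, replace LOCF as the primary method for the full analysis set with one of these:

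- a repeated-measures mixed model on all scheduled NRS visits to week 12, with baseline, centre and treatment-by-visit terms, reporting the week-12 contrast; or
- multiple imputation followed by ANCOVA at week 12.

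Add a delta-adjusted (tipping-point) sensitivity analysis that varies the shift separately by arm, and amend {20b} to allow it. LOCF may stay as a labelled sensitivity analysis. Remove or reword the sentence that holds end-point numbers equal to starting numbers, so that reports show how many week-12 scores were observed.

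The cost is protocol or analysis-plan wording and a little more programming, using visits already scheduled. The trade-off is reliance on a missing-at-random assumption in the primary analysis; the delta-adjusted analysis shows how far the conclusion depends on it.

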#### Assignment of interventions: randomization

##### Sequence generation {16a}

In this project, a multicenter positive-controlled, randomized clinical trial design is adopted, and subjects who meet the test and research criteria are randomly divided into two groups (proportion of 1:1), which are the trial group and the control group. The random number table was generated by special statistical staff at Shanghai University of T.C.M. According to strict random procedures by using the SAS software (version 9.4, SAS Company, Cary, NC, USA). The randomized list is stored on a secure database (Microsoft Office Access 2007) by the data manager and is inaccessible by the relevant case observer or other researchers. Each subject can only register and randomize once, and no detailed information about the subject can be deleted from the database.

The design procedures of the specific randomized scheme of multicenter clinical trials include randomized parameter setting, randomized regulations, SAS-randomized program design, and the resulting random numbers, randomized coding of the trial center, randomized coding of the trial cases, and randomized coding of the treatment group.
Randomization parameter setting

Seed number, the initial value of the random number, in this study is 151427.

The total number of cases is the sample size. Area group length × area group number = total number of cases: sample size 240 cases, area group length 4, and area group number 60.

Stratification number, taking the center (hospital) participating in the clinical trial as the stratification factor, because the number of cases completed by each participating clinical trial center cannot be determined in advance, the management method of “random center” is adopted in this study; that is, when subjects are enrolled, the person in charge of each participating research center immediately requests the random number and corresponding group code from the “random center” by telephone.

The number of test groups is divided into trial group and control group.

Distribution proportion, the number of samples in each treatment group, is allocated by 1:1.
(2)Randomization rules

Randomization rules for center code distribution

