##### Methods for additional analyses (e.g., subgroup analyses) {20b}

There will be no other additional analyses beyond the main analyses for the primary and secondary outcomes.

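### Primary pain analysis: within-arm paired tests and single-factor ANOVA at six visits, with week 12 not named as the one deciding between-group comparison

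*Protocol article*

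**What the plan says.** The outcomes section (Effectiveness evaluation index) states that "cervical pain is the primary observation index, measured by NRS", without naming a primary visit there. Objective {7}, the abstract and the Discussion state a between-group hypothesis: that manipulation has advantages over NSAIDs.

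Sample size {14} does use one visit: "the first observation index after 12 weeks of treatment was NRS score of neck pain". It gives 1.50 ± 1.70 against 2.08 ± 1.65, two-sided α = 0.05, β = 0.10, a boundary value of 0.08, 102 cases, and 120 per group after allowing for loss.

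Statistical methods {20a} then sets out the pain analysis in two steps. The first is a paired t "test statistical analysis is carried out for each group’s pre-treatment pain and the improvement of each group’s pain after treatment intervention". The second is that "single-factor analysis of variance is carried out for each group’s immediate, 3-day, 1-, 2-, 4-, 12-week pain after intervention". For the secondary outcomes, "One-way ANOVA is used to analyze the cervical dysfunction index, cervical activity, overall improvement, and treatment satisfaction of patients at 12 weeks". The section closes with "All the statistical tests are double-sided" and a threshold of P < 0.05. It gives no multiplicity rule, no covariate and no centre term. Section {20b} adds: "There will be no other additional analyses beyond the main analyses for the primary and secondary outcomes".

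Two design features bear on this. Randomisation is stratified by hospital, "taking the center (hospital) participating in the clinical trial as the stratification factor". Section {20a} also defines baseline as the last value before first treatment and fills missing values of the main variable by LOCF, so that the number evaluated at the end matches the number at the start.

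**The concern.** The trial asks whether one treatment relieves pain better than the other. As written, the analysis section never states the single comparison that answers this.

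- **Paired tests.** Patients enter with neck pain of under 12 weeks and NRS of at least 3. Both arms can be expected to improve through natural recovery and regression to the mean. Significant improvement in one arm or both says nothing about the difference between them.
- **ANOVA of pain.** The words referring to each group's pain leave open whether arms are compared at each visit or visits are compared within an arm. The first gives six chances of a significant result. The second gives no treatment comparison and ignores that the same patients are measured repeatedly.
- **Unused information.** Baseline NRS is collected and centre is the stratification factor, but a single-factor analysis uses neither.
- **Satisfaction.** ANOVA is prescribed for an item with three ordered levels. This is a smaller, secondary matter.

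At stake is whether a reported superiority on pain rests on one pre-stated test, or on whichever visit or within-arm change happened to reach P < 0.05.

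**Working it through.** **Inputs from Sample size {14}.** Difference = 2.08 − 1.50 = 0.58. Pooled SD = √[(1.70² + 1.65²)/2] = 1.675.

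**The plan's own figure.** n per arm = 2 × SD² × (1.960 + 1.282)² / 0.58² = 176 at two-sided 0.05 and 90% power, not 102. With the boundary value added (0.58 + 0.08 = 0.66) it is 136. The figure of 102 per arm appears with 0.66 and 80% power, which is not the stated β. This is a separate sample-size matter. It is noted only because the power figures below use the same inputs.

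**Paired tests.** Suppose both arms truly improve by the same amount and each paired test has power p. The chance that exactly one arm is significant is 2p(1 − p): 2 × 0.8 × 0.2 = 32% for p = 0.8, and 2 × 0.9 × 0.1 = 18% for p = 0.9. If improvement is large, both arms are significant whatever the treatment difference. Assume a 1-point mean improvement and an SD of change of 1.7 (neither is in the documents). Then t = 1/(1.7/√102) = 5.9 in each arm.

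**Reading A: ANOVA compares arms at each of six visits.** With independent tests, the chance of at least one P < 0.05 under no difference is 1 − 0.95⁶ = 26.5%. Visits are correlated, but the documents give no correlation. Simulation of six equally correlated z tests (400,000 draws) gives:

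| Assumed correlation | Any false difference | False difference favouring manipulation |
|---|---|---|
| 0.3 | 24.0% | 12.0% |
| 0.5 | 20.8% | 10.3% |
| 0.7 | 16.4% | 8.2% |
| 0.8 | 13.9% | 6.9% |

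The single-test references are 5% and 2.5%. These rates apply only if any visit may count as success. The text neither states nor prevents that.

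**Reading B: ANOVA runs across visits within an arm.** The table does not apply. Observations from the same patient are treated as independent, and section {20a} then contains no between-group pain test.

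**Precision of an unadjusted comparison of arms at week 12.** Power = Φ(0.58 / [1.675 × √(1 − r²) × √(2/n)] − 1.96), where r is the assumed correlation between baseline and week-12 NRS. The full analysis set with LOCF implies about n = 120 per arm; 102 is shown for comparison.

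| r (assumed) | n = 120 | n = 102 |
|---|---|---|
| unadjusted | 76.5% | 69.6% |
| 0.2 | 78.2% | 71.4% |
| 0.3 | 80.3% | 73.6% |
| 0.5 | 87.2% | 81.5% |
| 0.6 | 91.8% | 87.1% |

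These figures are for a superiority test of 0.58 and leave the boundary value aside.

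**The case against.** The case on the other side has real content.

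- **Week 12 is implied.** The trial is sized on it and NRS is consistently the primary outcome, so it would be wrong to say the document points to no visit. What stands is narrower: the analysis section lists week 12 last among six visits and gives it no special status.
- **The sentence is garbled.** The visit lists are unreliable (week 8 is a scheduled visit but missing for pain), and no single reading supports every criticism. That is correct. The false-positive rates belong to Reading A and the repeated-measures criticism to Reading B.
- **An unadjusted comparison is valid.** In a randomised trial, omitting baseline and centre costs precision but does not inflate type I error, and covariates are often left to an analysis plan. This stands, so adjustment is an improvement, not the repair of an invalid test. The gain may also be small: entry at NRS ≥ 3 and week-12 means near the floor can weaken the baseline correlation. At r = 0.1, power at 102 per arm moves only from 69.6% to 70.0%.
- **The trial is called exploratory.** Study setting {9} and the Discussion's limitations say so, which softens the multiplicity demand. But the abstract and the Discussion also say the aim is to confirm a hypothesis, and the size is set with formal α and β. Nor does the label turn a within-arm test into a comparison.

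A reader might infer that the trial's true superiority power is about 69%, or that its false-positive rate is 24%. The documents support neither as a flat statement. The first uses 102 per arm although the LOCF full analysis set implies about 120. The second counts errors in both directions, needs Reading A, and assumes that any visit may decide. A reader might also infer that the paired tests are meant to settle the between-group question, which the text does not say.

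**Conclusion.** The concern holds in this form: section {20a} fixes within-arm paired tests and single-factor ANOVAs of pain at six visits, each at 0.05, and does not make the week-12 between-group difference the single primary test. This is a stated method that does not match the stated hypothesis, so it is more than detail left to an unseen analysis plan.

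The size depends on the reading. If arms are compared at each visit and any visit may count, the chance of a false difference is about 24% to 14% (12% to 7% favouring manipulation), under assumed correlations of 0.3 to 0.8. If the ANOVA is within arm, no between-group pain test exists. The precision forgone at 120 per arm is the gap between 76.5% power and 78% to 92%, under an assumed baseline correlation of 0.2 to 0.6. The absence of a designated comparison rests on no assumed figure; the percentages do.

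**What to change.** In section {20a}, name the week-12 between-group difference in NRS as the single primary test. Estimate it by ANCOVA, or as the week-12 contrast of a repeated-measures mixed model, with treatment, baseline NRS and centre as terms. Test it two-sided at 0.05 and report the adjusted difference with its 95% CI. Make the other pain visits supportive, without significance claims, and report the paired before/after results descriptively only. Use the same adjusted model for the continuous secondary outcomes (NDI, cervical mobility, SF-36 scores), and a Wilcoxon or proportional-odds analysis for the three-level satisfaction item. Rewrite the ANOVA sentence so that it can be read only one way.

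The cost is a change of wording: no extra patients, visits or data, and the planned SPSS software fits these models. The downside is giving up significance claims at the non-primary visits.
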